### 8.3 Statistical issues

The goals of this pilot study are to assess the safety, feasibility, and potential for efficacy of RT-CGM as an adjunct to SMBG in conjunction with insulin pump therapy to produce improved glycemic control in a small sample of diabetic patients with gastroparesis. The findings are intended to provide the foundation

for determination of whether a large multicenter randomized, controlled efficacy trial of RT-CGMS as an adjunct to SMBG in conjunction with insulin pump therapy vs. conventional diabetes management should be conducted in diabetic patients with symptomatic gastroparesis. The current study will provide valuable pilot data to inform the design of an efficacy trial.

As noted above, the primary safety outcome measure for our study is the weekly frequency of mild, moderate and severe hypoglycemic episodes. There is very limited (published or from other sources) information on the frequency of mild, moderate and severe hypoglycemic events in tightly controlled diabetic gastroparesis. Thus, for planning purposes, we relied upon a consensus of the clinical experiences of the investigators ([name], [name], and [name]) for estimates needed for the statistical design of this pilot study:

- Assumed mean weekly mild to moderate hypoglycemic episodes by SMBG: 0.6
- Assumed SD for weekly mild to moderate hypoglycemic episodes by meter glucose: 0.8
- Assumed intra-class correlation between baseline and on-treatment weekly mild, moderate and severe hypoglycemic episodes by meter glucose: 0.6
- Estimated variance of change from baseline (a minimum of 4 weeks up to 16 weeks) to on-treatment (24 weeks) mean weekly mild, moderate and severe hypoglycemic episodes (estimated from SD and intraclass correlation, accounting for 3:1 ratio of on-treatment to baseline period).

We planned the study to test the safety hypothesis that, compared to a minimum of 4 weeks up to 16 weeks of baseline treatment, any increase in mean weekly mild, moderate and severe hypoglycemic events during approximately 24 weeks of insulin pump treatment and RT-CGM was no larger than 35%. Using a one-sample equivalence z-test and assuming one-sided Type I error of 0.05, power =0.9, expected percent increase from baseline to on-treatment=0%, and equivalence limit of 35% (0.6 vs. 0.81 episodes per week), the calculated sample size was N=37. The method of calculation and software used are as follows:

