- Method for sample size calculation: One sample test for equivalence (Chow, Shao and Wang, Sample Size Calculations In Clinical Research, Taylor & Francis, NY, 2003: p.52-53)23
- Software: Centre for Clinical Trials, Chinese University of Hong Kong24  
[http://www.cct.cuhk.edu.hk/stat/mean/osm\\_equivalence.htm](http://www.cct.cuhk.edu.hk/stat/mean/osm_equivalence.htm)

We increased the target sample size approximately 10% to N=40 patients to allow departures from assumptions. In addition, we plan to review safety data only with the DSMB when approximately N=10 patients have completed the study. The DSMB will advise on whether or not it is safe to proceed towards the full sample size of 40 patients.

An important, but secondary, efficacy outcome is reduction in hemoglobin A1c. However, if we assume that 25% (10 patients) do not achieve good glycemic control (hemoglobin A1c >7% at 12 and 24-weeks), the confidence limits on the actual proportion not achieving good control with 40 patients will be wide with a half-width of  $\pm 16\%$ . A sample size of 40 will provide adequate power to detect clinically meaningful changes in some measures of gastroparesis symptoms, quality of life, or on measures of gastric motor and sensory and autonomic function in this pilot study; however, a larger, study with a control group would be needed to provide evidence of efficacy. A 25% reduction in mean from a baseline GCSI score of  $27 \pm 15$  to  $20 \pm 15$ , with a sample size of 40, can be detected with >99% power, again assuming a Type I error of 0.05 and a modest intra-class correlation between baseline and follow-up GCSI measures. Comparisons within GLUMIT-DG subgroups will have limited statistical power; for example, we will compare Type 1 versus Type 2 diabetics for indications of differential outcomes,

however, the power for such comparisons will be low -- only 57% power for the primary hypoglycemic outcome measure with equal numbers of Type 1 or type 2 diabetics and less power if the numbers are unequal.

Questions of efficacy and subgroup comparisons for differential responses are best addressed in the context of a larger multicenter, randomized, controlled trial; however, the GLUMIT-DG pilot study will provide key information on variability in outcome measures at baseline and over time, and on the potential effect sizes - this information is not currently available for other sources and is needed to inform trial design.

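### The stated power above 99% for the GCSI change does not follow from a 27 to 20 fall, SD 15, N=40 and a modest correlation

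*Protocol*

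**What the plan says.** Section 8.3 of the protocol sizes the study on weekly hypoglycemic episodes and then comments on what 40 patients can show for secondary outcomes. For symptoms it gives one worked example, a fall of a quarter in the mean GCSI, 27±15 before and 20±15 after. Of this change in 40 patients it says that it "can be detected with >99% power, again assuming a Type I error of 0.05 and a modest intra-class correlation". No number is attached to *modest*, and the sentence does not say whether the test is one- or two-sided.

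Two other statements in section 8.3 bear on those gaps. The primary calculation is made "assuming one-sided Type I error of 0.05, power =0.9", the only Type I error given before the GCSI sentence. The only correlation with a value is the one for the primary outcome: "Assumed intra-class correlation between baseline and on-treatment weekly mild, moderate and severe hypoglycemic episodes by meter glucose: 0.6".

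**The concern.** All inputs but the correlation are printed, so the claim can be checked. A 7-point difference against an SD of 15 is just under half an SD at a single time point. With 40 patients measured before and after, that effect gives more than 99% power only if the two measurements are strongly correlated.

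This is the only worked power figure behind the section's statement that 40 patients are enough to detect worthwhile change in some symptom, quality-of-life and physiological measures. Power above 99% implies a chance below 1 in 100 of missing a true 7-point fall. If the real chance is between 1 in 20 and 1 in 3, a non-significant GCSI change carries much less information than the text suggests. The error runs in the favourable direction.

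**Working it through.** **Inputs, all from section 8.3 unless noted**
- Mean GCSI 27 at baseline and 20 at follow-up, so a difference of 7. An exact 25% of 27 is 6.75.
- SD 15 at both times; n = 40; Type I error 0.05, sidedness not given in this sentence.
- ICC not given. Assumed range for this check: 0.3 to 0.6. The upper end is the value the protocol uses for hypoglycemic episodes.
- Design: one uncontrolled group compared with its own baseline (section 3.1).

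**Formulas**
- SD of change = √(15² + 15² − 2·ICC·15²) = 15·√(2(1−ICC)).
- Noncentrality = 7·√40 / SD of change = 44.27 / SD of change.
- Power from the noncentral t with 39 degrees of freedom; critical value 2.023 two-sided, 1.685 one-sided.

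**Results for a difference of 7**

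| ICC | SD of change | Noncentrality | Power, two-sided | Power, one-sided |
|---|---|---|---|---|
| 0.3 | 17.75 | 2.49 | 68.2% | 79.0% |
| 0.5 | 15.00 | 2.95 | 82.1% | 89.5% |
| 0.6 | 13.42 | 3.30 | 89.6% | 94.5% |

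The chance of missing a true 7-point fall is therefore about 32%, 18% and 10% two-sided, or 21%, 10.5% and 5.5% one-sided, against the implied figure of under 1%. With the exact 25% fall of 6.75 points, two-sided power drops to 65%, 79% and 87%.

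**Attempt to reproduce the printed figure**
- *Solving for the ICC.* By the normal approximation, 99% power two-sided needs an SD of change of 44.27/(1.960+2.326) = 10.33, so ICC = 1 − 10.33²/450 = 0.76. One-sided it is 44.27/(1.645+2.326) = 11.15, so ICC = 0.72. With the noncentral t the limits are 10.07 and 10.95, so ICC = 0.775 and 0.733.
- *z-test instead of t.* At ICC 0.6: 91.0% two-sided, 95.1% one-sided.
- *Averaging weeks 12 and 24.* With the same ICC between all pairs of visits, the SD of change is 15·√(1.5(1−ICC)), or 11.62 at ICC 0.6. Power (t) is 96.0% two-sided and 98.2% one-sided; the one-sided z-test gives 98.5%. This version passes 99% only at an ICC of about 0.68 two-sided or 0.63 one-sided (z).
- *Baseline mean treated as fixed, SD 15 (z).* 84% two-sided, 90% one-sided.

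None of these reaches 99% at an ICC of 0.6 or below.

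**What SD would be needed instead**
Dividing the allowable SD of change (10.07 two-sided, 10.95 one-sided) by √(2(1−ICC)) gives the common SD at which 99% is reached: 11.3 or 12.2 at ICC 0.6, 10.1 or 11.0 at ICC 0.5, and 8.5 or 9.3 at ICC 0.3. All are well below the printed 15.

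**The case against.** The strongest defence is that the sentence leaves its inputs open. The reference back to the earlier Type I error can fairly be read as one-sided 0.05, the correlation is not numbered, and the analysis might average two follow-up visits. All of this is right, and it means a reader should not conclude that the correct figure is 68% to 90%. That range rests on a two-sided test and on ICC 0.3 to 0.6, neither of which the protocol states; one-sided, the range is about 79% to 94%. But these gaps affect only which replacement is right. The most favourable combination at ICC 0.6 stays below 99%.

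A second defence is that the effect on the study is small. GCSI is a secondary outcome, N=40 comes from the hypoglycemia calculation, and section 8.3 itself says a larger controlled study would be needed for evidence of efficacy. This stands. A reader might infer that the pilot is underpowered for symptoms or that a null result will be misread, but the documents do not establish either. At ICC 0.5 to 0.6 the power is 82% to 90% two-sided, so the general statement of adequate power survives there. It falls below the usual 80% only at lower correlations.

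A reader might also infer that the HbA1c statement in the same paragraph is wrong, since "if we assume that 25% (10 patients) do not achieve good glycemic control" gives a symmetric 95% half-width of 1.96·√(0.25·0.75/40) = 13.4 points, not the printed ±16. The documents do not support that. No confidence level or method is stated, and the exact 95% interval for 10 of 40 is 12.7% to 41.2%, whose upper arm is 16.2 points. The printed value is consistent with quoting the wider arm, it is cautious, and it serves only to say that the limits are wide. Replacing it with ±13% would understate the upper uncertainty.

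**Conclusion.** The GCSI power statement is wrong as written. With a 7-point difference, SD 15 at both times and 40 patients, power above 99% requires a baseline to follow-up correlation of about 0.775 two-sided or 0.73 one-sided. Over an assumed ICC of 0.3 to 0.6 the power is about 68% to 90% two-sided, or 79% to 94% one-sided.

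This assumes a paired comparison of one follow-up score with baseline, equal SDs at both times as printed, approximate normality and all 40 patients contributing; missing follow-up scores would lower the power. The conclusion about the printed figure does not depend on sidedness, on the choice of z or t, or on averaging the two follow-up visits. The replacement figure does depend on the ICC and sidedness, which only the sponsor can supply. The finding does not reach the sample size, the primary analysis or the HbA1c half-width.

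**What to change.** In section 8.3, state the ICC assumed for GCSI and whether the test is one- or two-sided, and replace the printed figure with the matching power. If no single ICC can be defended, give the range, for example: about 68% to 90% two-sided, or 79% to 94% one-sided, for ICC 0.3 to 0.6.

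If the authors had a smaller SD in mind because entry requires a GCSI of at least 18 (section 4.2), they should print that SD in place of 15 and recompute. The same entry floor would tend to lower the correlation, so the two should be chosen together.

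The cost is one reworded sentence and a less favourable figure. N stays at 40 and no analysis changes.

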### Sample size and statistical analysis of primary outcome

- A total of 40 patients will be enrolled in this pilot study
- Rationale for sample size
  - Primary safety outcome: weekly frequency of mild, moderate, or severe hypoglycemic episodes by discrete glucose meter values and/or a reference blood glucose level if the subject is seen in a hospital (emergency room)
  - Assumed mean weekly mild, moderate, or severe hypoglycemic episodes by discrete glucose values: 0.6
  - Assumed SD for weekly mild, moderate, or severe hypoglycemic episodes by discrete glucose values: 0.8
  - Assumed intra-class correlation between baseline and on-treatment weekly mild, moderate, or severe hypoglycemic episodes by discrete glucose values: 0.6
  - Estimated variance of change from baseline (a minimum of 4 weeks up to 16 weeks) to on-treatment (24 weeks) mean weekly mild, moderate, or severe hypoglycemic episodes (estimated from SD and intraclass correlation, accounting for 3:1 ratio of on-treatment to baseline period lengths): 0.41
  - Type I error: 0.05 (1-sided for equivalence)
  - Power: 0.9
  - Expected percent increase from baseline in mean weekly mild, moderate, or severe hypoglycemic episodes during the treatment period with RT-CGM while using the

- glucose pump: 0%
- Equivalence limit (maximum percent increase in mean weekly mild, moderate, or severe hypoglycemic episodes): 35% (0.6 vs. 0.81 episodes per week)
- Method for sample size calculation: One sample test for equivalence (Chow, Shao and Wang, Sample Size Calculations In Clinical Research, Taylor & Francis, NY, 2003: p. 52-53)
- Software: Centre for Clinical Trials, Chinese University of Hong Kong -- [http://www.cct.cuhk.edu.hk/stat/mean/osm\\_equivalence.htm](http://www.cct.cuhk.edu.hk/stat/mean/osm_equivalence.htm)
- Calculated sample size: N = 37

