**Recruitment**

- 20 type 1 and 20 type 2 diabetics with gastroparesis will be enrolled at 7 clinical centers
- 30 month period
- Enrollment of 10 patients at the Wake Forest University clinical center
- Enrollment of 5 patients per clinical center expected at the remaining 6 clinical centers

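### The 57% power given for comparing Type 1 with Type 2 diabetics does not match a two-group comparison at the stated variance; it matches a one-sample equivalence test in 20 patients

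*Protocol*

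**What the plan says.** The sample size is built on a single method, given in the Design synopsis and again in section 8.3: "Method for sample size calculation: One sample test for equivalence". Section 8.3 sets it up as "assuming one-sided Type I error of 0.05, power =0.9", with "expected percent increase from baseline to on-treatment=0" percent and an "equivalence limit of 35% (0.6 vs. 0.81 episodes per week"), and arrives at N=37, raised to 40. The synopsis gives the variance of the change from baseline as 0.41.

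On the two diabetes types, the synopsis (Recruitment) says "20 type 1 and 20 type 2 diabetics with gastroparesis will be enrolled at 7 clinical centers". Section 8.3 then says "we will compare Type 1 versus Type 2 diabetics for indications of differential outcomes", warns that power will be low, and quantifies it: "only 57% power for the primary hypoglycemic outcome measure with equal numbers of Type 1 or type 2 diabetics". It adds that imbalance between the groups would reduce the power further. It names no test, no sidedness and no between-type difference for this figure.

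**The concern.** Comparing the change in one group of 20 with the change in another carries twice the variance of testing a single group of 20 against its own baseline. A power figure for the comparison between types should reflect that, and should refer to a stated difference between them. The 57% does neither. It is close to what the one-sample formula behind N=37 gives when n is set to 20.

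At stake is how a reader weighs a null result. A power of 57% suggests that a relevant difference between types would be found slightly more often than not. If the real figure is lower, similar hypoglycemia rates in the two types say less than the protocol implies. The study is meant to inform the design of a later randomized trial, so the printed figure should belong to the comparison it describes.

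**Working it through.** **Inputs.** Variance of change 0.41 (Design synopsis, sample size). One-sided alpha 0.05, expected change 0%, and a limit of 35%, printed as 0.6 vs 0.81, i.e. 0.81 − 0.6 = 0.21 episodes per week (section 8.3). Subgroups of 20 and 20 (Recruitment). The between-type difference is not given. I assume 0.21 (the printed limit) and 0.35 (the value that reproduces the protocol's figures) and show both. Sidedness is not given for this comparison either, so both are shown.

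**Step 1: reproduce the protocol's figures.** For a one-sample equivalence z-test with true change zero:

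- N = variance × (z₀.₉₅ + z₁₋β/₂)² / margin². With margin 0.35: 0.41 × (1.645 + 1.645)² / 0.35² = 36.2, rounded up to 37, as stated.
- Power = 2Φ(margin / √(variance/n) − 1.645) − 1. With n = 20 and margin 0.35: 0.35 / √(0.41/20) = 2.444, and 2Φ(0.799) − 1 = 57.6%.

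So 35% entered as 0.35 reproduces both printed numbers. With the printed limit of 0.21 and variance 0.41, the same formulas give N = 100.6 (101) and, at n = 20, a power of 0% (42.9% if only the upper bound is tested). A second route also lands near 57%. If the margin is 0.21, N=37 implies an SD of 0.388, and the one-sample power at n = 20 is then 56.1%. Both routes describe equivalence to baseline within one group of 20.

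**Step 2: the two-group comparison, 20 vs 20, variance 0.41.** The variance of the difference in mean change is 0.41 × (1/20 + 1/20) = 0.041, twice the one-sample value of 0.0205. The standard error is √0.041 = 0.2025.

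| Difference (episodes/week) | Difference / SE | Two-sided power (z; t) | One-sided power (z; t) |
|---|---|---|---|
| 0.21 | 1.037 | 17.8%; 17.1% | 27.2%; 26.6% |
| 0.35 | 1.728 | 40.8%; 39.2% | 53.3%; 52.1% |

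A two-group equivalence test gives 0% with margin 0.21 and 6.7% with margin 0.35. None of these is 57%. With the SD of 0.388 from the second route and a difference of 0.21, two-group power is 40.1% two-sided and 52.6% one-sided.

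**Step 3: the difference that would give 57%.** With z₀.₅₇ = 0.176:

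- One-sided: (1.645 + 0.176) × 0.2025 = 0.37 episodes per week.
- Two-sided: (1.960 + 0.176) × 0.2025 = 0.43 episodes per week.

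These are about 61% and 72% of the assumed mean of 0.6.

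**Step 4: separate the two sources of the gap.** Keeping the inputs that yield 57.6% and changing only the test from one-sample to two-group gives 39-53%. The further fall to 17-27% comes from using 0.21 instead of 0.35, which is the conflict in the main sample size and not the choice of test.

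**The case against.** The strongest reply has four parts.

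- **The source of the 57% is inferred.** The protocol does not say how it was computed, and other unstated inputs come close. A one-sided two-group t-test with difference 0.35 and variance 0.341 (0.64 × 0.4 × 4/3) gives 58.5%. One with difference 0.42 and variance 0.512 (2 × 0.64 × 0.4) gives 57.1%. This stands as a caution. Neither variance is the printed 0.41, however, and the one-sample inputs reproduce N=37 as well.
- **The sentence may describe power within each type.** The remark on unequal numbers does not rule this out, because the smaller subgroup would lose power there too. But the sentence attaches the figure to comparisons between types. If within-type power was meant, the label is wrong and still needs correcting.
- **A one-sided reading shrinks the error.** One-sided 0.05 is the only sidedness stated for this outcome. With 0.35 kept, two-group power is 52-53%, only 4 to 5 points below 57%. That is fair. It depends on a difference of 0.35 episodes per week, which the protocol nowhere prints as its limit.
- **The protocol already says the power is low.** It treats the comparison as looking for indications and defers subgroup questions to a larger randomized trial. This stands and limits the consequence.

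**Conclusion.** The 57% does not belong to a Type 1 versus Type 2 comparison at the stated variance of 0.41 for either difference that the protocol's figures suggest. At alpha 0.05 with 20 per group, two-group power is about 39-41% two-sided or 52-53% one-sided for 0.35 episodes per week, and about 17-18% or 27% for 0.21. These values rest on the printed variance and on a difference that I had to assume.

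A reader might infer that the comparison simply has 17-27% power. The protocol does not support that, because it names no between-type difference, and part of the fall comes from the separate 0.35-versus-0.21 conflict. Nor does it say that the equal enrolment was chosen for the sake of this comparison, or that its result will decide whether the types are pooled in a later trial. The sample size of 40, the primary test and the monitoring rule are untouched by this point. What remains is an incorrect or mislabelled power statement of modest consequence.

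**What to change.** First reconcile the limit used in the main sample size: 35% of 0.6 is 0.21, but N=37 at variance 0.41 follows only from 0.35.

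Then amend the sentence in section 8.3 in one of two ways:

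- Replace the 57% with the power of the two-group comparison, and state the between-type difference, the variance and the sidedness. For example, at variance 0.41 with 20 per group and two-sided alpha 0.05, power is 17-18% for a difference of 0.21 episodes per week and 39-41% for 0.35.
- Keep the 57%, but label it as the power of an equivalence test against baseline within one diabetes type of 20 patients, with the inputs actually used.

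The cost of this point is one reworded sentence, with no extra patients, data or procedures. Under the first option the stated power becomes less favourable.

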#### **8.4 Interim analysis**

An independent Data and Safety Monitoring Board (DSMB), appointed by the NIDDK, is responsible for providing input to the NIDDK regarding approval of the protocol for the GLUMIT-DG study and for monitoring the accumulated interim data as the study progresses to assess patient safety and data quality and to review efficacy. The DSMB is a multi-disciplinary group with a written charge provided by the NIDDK. The DSMB serves in a consultative capacity to the NIDDK, which will communicate with the investigators regarding the DSMB deliberations.

The DSMB meets to provide input to the NIDDK regarding approval of the protocol and supporting documents. After the study commences, the DSMB meets twice a year to review safety data and other performance issues. The DSMB may request more frequent meetings if necessary to fulfill its charge or at the discretion of the NIDDK Program Official. It may also request additional safety reports on a more frequent basis. For example, all serious adverse events are reported to the DSMB quarterly for their consideration and recommendations as they occur. The DSMB Charter provides more specific information and defines the roles, responsibilities, and activities of the DSMB.

The DSMB will review safety data when ten patients (N=10) have completed the study. The DSMB will advise on whether or not it is safe to proceed towards the full sample size of 40 patients.

No formal stopping guidelines are proposed for this pilot study of safety. However, each DSMB periodic monitoring report will include an analysis of the primary safety outcome that calculates, based on the available data, the lower 95% confidence limit on the estimated percent increase from baseline in mean weekly mild to moderate or severe hypoglycemic events during the on-treatment period. If the lower confidence limit is greater than 35%, the DSMB will be asked to discuss and vote on whether the study should continue, based on a review of all information available at that time.

---

